##### 2. Genotyping

Whole blood for DNA extraction, and for DNA and lymphoblast banking at the Rutgers Cell & DNA Repository (http://www.rucdr.org/), is collected from every consenting patient at the screening visit. DNA will be used for genotyping genetic polymorphisms, mostly single nucleotide polymorphisms (SNPs), within the CRH receptor (*CRHR1*) gene and other stress-related candidate genes that emerge from previous human or animal studies, including genes from the HPA axis, monoaminergic systems, or neurotrophic systems. The study was not powered to test for genome-wide associations; however, data from it might be useful in meta-analyses across studies.

##### 3. Gene expression profiles

Whole blood collected in Tempus blood RNA tubes (Applied Biosystems, Grand Island, NY, USA) is collected for RNA at Visit 2 prior to randomization and at Visit 7, after five weeks on the study medication. Expression of specific candidate transcripts encoding chaperone and co-chaperone proteins of the glucocorticoid receptor, using real-time PCR as well as gene-expression microarrays, will be performed. We will assess the correlation of these gene-expression patterns with other putative biomarkers (for example, the dexamethasone suppression test) to evaluate whether they can be used to predict or mediate change during treatment.

##### 4. Neuroendocrine evaluation

Salivary samples are a validated means of non-invasively estimating circadian cortisol rhythms and of monitoring the dexamethasone suppression response for use as a marker of PTSD. At Visit 1, subjects are given pre-labeled Salivette collection tubes (Sarstedt, Rommesldorf, Germany) and instructed in the sample collection process. On the morning of Visit 2, one day prior to randomization, participants collect three salivary samples: (1) immediately upon awakening (and prior to eating); (2) 30 minutes after awakening, and (3) 60 minutes after awakening. Participants come to the clinic for Visit 2 at 8 am for the venipuncture collection of plasma cortisol and ACTH levels. Upon completion of Visit 2, participants are given two more Salivettes and one pill of dexamethasone 0.5 mg. On the night of Visit 2, participants collect the fourth salivary sample at 11 pm, followed immediately by ingestion of the dexamethasone. On the morning of Visit 3, subjects collect the fifth salivary sample upon awakening and return to the clinic at 8 am for the post-dexamethasone venipuncture for plasma cortisol and ACTH levels. This two-day procedure is repeated at Visits 7 and 8 in order to assess change in the neuroendocrine measures after five weeks on study medication. Due to confounding of HPA measures stemming from altered circadian rhythms, night-shift workers do not complete this component of the study.

#### B. Neuropsychological assessments

We will assess the cognitive and functional ability of participants at Visit 1, prior to randomization, and again at Visit 7, after five weeks on study medication.

##### 1. Neuropsychological battery

The MATRICS Consensus Cognitive Battery (MCCB), excluding the Social Cognition assessment portion, is used to assess for neuropsychological (NP) impairment [38]. This assessment can detect both improvements in NP performance if any occur, but also unanticipated worsening, if any, because of the lack of floor effects in the assessment. The MATRICS Battery includes ten different standard NP tests, which are administered with standard instructions and have extensive normative standards available. The tests include: Category Fluency; Brief Assessment of Cognition in Schizophrenia Symbol Coding; Trail-Making Test, Part A; Continuous Performance Test, Identical Pairs Version; University of Maryland Letter-Number Span; Wechsler Memory Scale-III Spatial Span; Hopkins Verbal Learning Test-R; Brief Visual Memory Test-Revised; and Neuropsychological Assessment Battery Mazes.

##### 2. Performance based-measures of functional capacity

The assessment of functional capacity uses instruments previously developed for use by patients with schizophrenia: the UCSD performance-based skills assessment (UPSA) [39]. The UPSA-B is an abbreviated version of the UPSA that involves role-play tasks similar in complexity to those that a community-dwelling person is likely to encounter and can be administered in ten minutes. The UPSA-B’s two domains result in a summary score ranging from 0 to 100.

#### C. Cross-site calibration

Calibration of clinical, psychophysiological and neuropsychological measures was conducted prior to beginning enrollment at each site and periodically through the trial. The lead investigators for the psychophysiological and neuropsychological components personally trained each site’s personnel in the testing procedures and actively monitor the quality of data collection through the trial. In addition, study administration, conduct, and recruitment are addressed in monthly conference calls involving each site’s principal investigator, project leads, and associated study staff.

### Randomization

Randomization occurs at Visit 3. To prevent confounding of the biological measures by the dexamethasone dose on the night before Visit 3, baseline laboratory and ECG tests are conducted the day prior at Visit 2. At Visit 3, upon completion of the post-dexamethasone venipuncture, participants are assessed with the CAPS, MADRS, C-SSRS, and CGI-S. To be eligible for randomization, participants have to score ≥ 50 on the CAPS rating for both the past week and the past month at this visit. At this visit subjects also complete the PSS-SR, QIDS-SR, the Pittsburgh Sleep Quality Index (PSQI) [40], Brief Pain Inventory (BPI) [41], and Patient Rated Inventory of Side Effects (PRISE) [42]. Self-reported functioning is assessed using the Sheehan Disability Scale (SDS) [43]. To assess the impact of recent significant life events, participants also complete the Life Experiences Survey (LES) [44].

Participants who meet all inclusion and no exclusion criteria are eligible for randomization. Treatment assignment lists, generated using randomized permuted blocks for each site, are used at each site to ensure equal allocation across treatment groups across the sites and at any time during the study. These lists were individually printed, placed in sealed opaque envelopes by the study biostatistician, and then delivered directly to the Investigational Drug Pharmacy personnel at each site. When a participant completes all procedures necessary for randomization, the study physician at each site notifies the pharmacy personnel, who assign the patient to the treatment group indicated on the randomization list.

### Protocol treatments

GlaxoSmithKline provided the study medication and matching placebo at no cost to the study. Bulk-shipped medication received at the Emory Investigational Drug Service is shipped as needed to the other sites’ investigational pharmacies. Medication throughout the trial is fixed at 350 mg nightly. The medication is formulated as white tablets, in two strengths: 50 mg and 100 mg, dispensed in separate bottles. Subjects take three of the 100 mg and one of the 50 mg tablets nightly between 6 and 8 pm, and record their dosing dates and times in a simple diary.

Pharmacokinetic measures of GSK561679 are assessed from single sample plasma collections at Visits 4, 5, 6, 9 and 11, and stored at −80°C until analyzed. Each participant’s pharmacokinetic samples are batch processed after their study participation is completed; consequently, they will not be used to guide dosing decisions or identify non-adherent subjects during their study treatment. Results from the analyses will be unblinded after finalizing all clinical trial data to identify: 1) whether any subjects did not take the study medication, and 2) to evaluate for associations between blood concentration and clinical effects.

### Study assessment visits

Symptom severity ratings are performed at weeks 1, 2, 4, and 6 post-randomization. At each of these visits, participants complete the PSS-SR, and QIDS-SR to assess PTSD and depressive symptom severity, respectively. A qualified rater administers the CAPS (for the past week), MADRS, and C-SSRS and all subjects also meet with a study psychiatrist for assessment of CGIs, concomitant medications, and adverse events. Additional self-report measures repeated at the week 6 post-randomization visit include the BPI, PSQI, LES and SDS. Vital signs are assessed at each visit and laboratory testing, particularly for liver enzyme changes, is conducted throughout the trial according to the schedule in Table 1. Side effect burden is assessed through physician inquiry and patient completion of the PRISE and the Frequency, Intensity, and Burden of Side Effects Rating (FIBSER) [42].

### Follow-up period

All participants who complete the six-week treatment phase or who terminate the trial early will return to the clinic 7 days (Visit 10) and 1 month (Visit 11) after their last dose of study medication. At these visits, rating scales and questionnaires of symptom severity, adverse events, and changes to concomitant medications are assessed, as identified in Table 1. Subjects with clinically significant abnormal laboratory tests or ECG findings at Visit 9 have those tests repeated at these follow-up visits. Upon study completion, all participants receive assistance in transitioning to another care provider as clinically appropriate at the research site (if they choose to do so) or are referred back to their physician.

### Major endpoints

The primary outcome is mean change on the CAPS past-week score between the two treatment arms. Secondary outcomes include response and remission on the CAPS past-week score. Response is defined as ≥ 50% reduction from the baseline CAPS total score at the final on-drug study visit (V9 for completers). Remission is defined as a CAPS score ≤ 20 at the final on-drug visit.

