**Methods/design:**

Currently untreated adult women, ages 18 to 65 years, with a primary psychiatric diagnosis of PTSD of at least 3 months’ duration, are being enrolled in a parallel-group, double-blind, placebo-controlled, randomized clinical trial evaluating the efficacy and safety of GSK561679, a novel CRHR1 receptor antagonist. GSK561679 (or matching placebo) is prescribed at a fixed dose of 350 mg nightly for six weeks. The primary trial hypothesis is that GSK561679 will reduce symptoms of PTSD, as measured by the Clinician-Administered PTSD Scale (CAPS), significantly more than placebo after six weeks of treatment. Putative biological markers of PTSD which may influence treatment response are measured prior to randomization and after five weeks’ exposure to the study medication, including: fear conditioning and extinction using psychophysiological measures; variants of stress-related genes and gene expression profiles; and indices of HPA axis reactivity. In addition, the impact of PTSD and treatment on neuropsychological performance and functional capacity are assessed at baseline and after the fifth week of study medication. After completion of the six-week double blind treatment period, subjects enter a one-month follow-up period to monitor for sustained response and resolution of any adverse effects.

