### Data analyses

#### Primary aim

##### Primary analysis

Our primary statistical analysis plan will be performed under the intent-to-treat (ITT) principle that utilizes a likelihood-based, mixed effects model that assumes any missing data meet the missing at random (MAR) assumption. Continuous variables will be fit using SAS PROC MIXED (SAS Institute Inc., Cary, NC, USA), and categorical data will be fit using the gllamm add-on to Stata [45]. Prior to model fitting, we will examine the distributions of the continuous outcome variables using visual inspection of histograms and boxplots to identify potential outliers. If variables are not normally distributed or contain outliers, then log transformations will be considered or appropriate nonparametric procedures will be substituted for the analyses stated. To address the possible increase in Type I errors due to multiple outcome variables, we have *a priori* selected a single outcome measure (CAPS total for past week) which will maintain the significance level (α) 0.05 for the primary analysis. For secondary outcome measures, we will adjust *P*-values by controlling for the false discovery rate [46] and report both unadjusted and adjusted *P*-values.

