#### Secondary aims

##### Response rates

We will use a mixed effects model for the binary response data (generalized linear mixed model or GLMM) where, at each time point, a subject will be classified as a responder if there is at least 50% improvement in CAPS compared to the baseline measure. The factors in the model will be the same as for testing the primary hypothesis above. This analysis is an averaged group comparison of time-point specific response rates, and thus a patient can change response categories over time. We anticipate observing a significant group-by-time interaction and will perform *post hoc* tests by time point to estimate when a significant divergence in response rates occurs.

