#### Statistical power/sample size

As this is the first trial of a CRHR1 antagonist in PTSD, we do not have any pilot data from which to estimate an effect size. Our sample size calculation of 154 subjects is based on an effect size of seven CAPS points, consistent with the observed difference in the study by Davidson and colleagues of the efficacy of sertraline for PTSD [48]. We used that study’s effect size and pooled between-subjects standard deviation, and expected early termination rates, to construct our power calculation on the specific test of the treatment group-by-time (two timepoints, pre and post) interaction effect for a standard repeated measures analysis of variance [49]. We used an alpha of 0.05 for all main effects and the interaction, and calculated that a sample size of 50 completers per group allows us to detect an interaction effect of this size with a power of 0.91. With the expected dropout rate of 35%, this requires recruitment of 77 subjects per group to meet the anticipated endpoint sample size, for a total randomized sample of 154 subjects.

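### The hypothesis is a CAPS difference after six weeks, but the primary outcome names no visit and the primary model names no deciding contrast; a baseline-adjusted Week 6 contrast should be named as the single primary test

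*Protocol article*

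**What the plan says.** The abstract (Methods/design) states the hypothesis with a time point: the drug is to reduce CAPS symptoms "significantly more than placebo after six weeks of treatment".

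The section Major endpoints gives the primary outcome without one: "The primary outcome is mean change on the CAPS past-week score between the two treatment arms". The same section ties response and remission, both secondary, to the final on-drug visit (V9 for completers).

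CAPS is measured repeatedly. Under Study assessment visits: "Symptom severity ratings are performed at weeks 1, 2, 4, and 6 post-randomization". Table 1 adds ratings at Visit 3 (baseline) and, in follow-up, at Weeks 7 and 10.

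The section Primary analysis says that the plan "utilizes a likelihood-based, mixed effects model that assumes any missing data meet the missing at random (MAR) assumption". It lists no factors, no baseline term and no deciding contrast.

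A group-by-time interaction involving CAPS appears in two other places:
- Statistical power/sample size bases the calculation on "the specific test of the treatment group-by-time (two timepoints, pre and post) interaction effect" in a repeated measures analysis of variance, with a seven-point effect, 50 completers per group and power 0.91.
- Response rates, a secondary analysis of binary response at each time point, says "The factors in the model will be the same as for testing the primary hypothesis above", although none are listed above. It continues "We anticipate observing a significant group-by-time interaction and will perform" tests at each time point post hoc.

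**The concern.** With four on-treatment CAPS visits, a mixed model can yield several legitimate tests: the treatment difference at Week 6, an overall treatment-by-visit interaction, a difference in slopes, or a treatment effect averaged over visits. These are different questions. The article controls type I error by choosing one outcome measure, but one scale with several possible contrasts is not yet one test at 0.05.

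The article's own pointers diverge. The hypothesis is a Week 6 difference. The powered test is a 1-df pre/post comparison. The only hint about the structure of the multi-visit model is an interaction followed by visit-wise tests of post hoc status. If the last pattern were carried over to the primary outcome, the trial could be declared positive with no drug-placebo difference at six weeks.

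There is also an efficiency question. The powered test compares raw change scores. Visit 3 CAPS is collected on everyone randomized and could be used as a covariate at no cost.

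**Working it through.** **Inputs from the article (Statistical power/sample size):** difference 7 CAPS points, 50 completers per group, alpha 0.05, power 0.91, dropout 35%. **Not given there, so assumed here:** two-sided testing, the SD of change, and the correlation rho between baseline and Week 6.

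**1. The article's own figures.** 50/0.65 = 76.9, so 77 per group and 154 in total, which matches. The power of 0.91 cannot be reproduced directly without an SD. Solved backwards for two groups of 50 (noncentral t), it implies an SD of change of about 10.5: standard error 10.5 × sqrt(2/50) = 2.1, noncentrality 7/2.1 = 3.33, power 0.91.

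**2. What the powered test is.** With two time points, the group-by-time F equals the squared two-sample t for change from baseline. A check on simulated data gave 3.954 for both. It is therefore a 1-df comparison of mean change. If the second time point is Week 6, it addresses the stated hypothesis.

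**3. What a multi-visit interaction would do.** Take Weeks 0, 1, 2, 4 and 6, 50 per group, SD of change 10.5 and compound symmetry. The within-subject error variance is 10.5²/2 = 55.1. The noncentrality is 25 × SS/55.1, where SS is the sum of squared deviations of the five group differences (baseline difference 0) from their mean. Power is from a 4-df F with 95 denominator df.

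| Difference at Weeks 1, 2, 4, 6 | SS | Noncentrality | Power |
|---|---|---|---|
| 7, 7, 3, 0 (nothing at Week 6) | 49.2 | 22.3 | 0.97 |
| 0, 0, 0, 7 (late only) | 39.2 | 17.8 | 0.93 |
| 7, 7, 7, 7 (early plateau) | 39.2 | 17.8 | 0.93 |
| 1.17, 2.33, 4.67, 7 (linear) | 31.6 | 14.3 | 0.86 |

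A large-sample chi-square reference gives 0.98 instead of 0.97 in the first row. Under an autoregressive correlation (rho 0.3 to 0.7 over six weeks), the linear profile falls to 0.74, while the late-only and plateau profiles rise to between 0.98 and 1.00. The comparator is 0.91 for the Week 6 change test. So the omnibus test can be significant with no Week 6 effect, and its power may be above or below plan.

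**4. Baseline adjustment.** The variance of the adjusted effect relative to the change-score effect is s1²(1 − rho²)/(s0² + s1² − 2·rho·s0·s1), where s0 is the baseline SD and s1 the Week 6 SD.
- Equal SDs: the ratio reduces to (1 + rho)/2, that is 0.65 to 0.85 for rho 0.3 to 0.7.
- Baseline compressed by the CAPS entry cut of 50 (assumed SD 15 to 16 against 20 to 25 at Week 6, rho 0.3 to 0.7): about 0.78 to 1.0. The lowest value is at SDs 16 and 20 with rho 0.3: 364/464 = 0.78. At SDs 15 and 25 with rho 0.6 it is 400/400 = 1.0, no gain.
- The ratio does not exceed 1.

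Power with equal SDs and SD of change 10.5, taking the residual SD as 10.5 × sqrt((1 + rho)/2): 0.98 (rho 0.3), 0.97 (0.5), 0.95 (0.7), 0.94 (0.8), against 0.91 unadjusted. If the SD of change were 20 (assumption), the figures would be 0.41 unadjusted and 0.45 to 0.58 adjusted over the same rho range.

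**The case against.** The strongest reply is that the article can be read as one consistent plan. The hypothesis is at six weeks, the outcome is the between-arm difference in mean change, and the powered pre/post interaction is exactly that difference. The interaction with post hoc visit tests belongs to the secondary response model. Sharing factors with the primary model does not mean sharing its deciding test. Fixed effects, covariance structure and the named contrast are details that an article commonly leaves to the full protocol or analysis plan.

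Much of this stands, and it rules out several stronger readings that a reader might infer:
- That the article makes an omnibus interaction its primary test. It does not; the section Primary analysis names no interaction.
- That the powered test fails to answer the question. It answers it if the second time point is Week 6.
- That the primary model excludes baseline CAPS. The article is silent. Only the test used for power is unadjusted.
- That power is lost against plan, for example to 0.76 on 4 df or 0.80 on 3 df. Those values give the omnibus test only the noncentrality of the single Week 6 contrast (about 10.9), which is the least it can have. They are lower bounds, nearly reached by the autoregressive linear profile. The 0.91 was computed for the two-timepoint interaction itself.

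The reply does not remove the ambiguity. The article times its secondary outcomes but not its primary one, and it refers back to model factors that it does not list. Where it does describe a multi-visit analysis, visit comparisons are post hoc.

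**Conclusion.** The point holds as a request to fix the deciding comparison. The hypothesis is dated, the primary outcome is not, and the primary model carries no stated contrast. The article's other sections point to two tests of different kinds. One of them, the pre/post interaction, serves the hypothesis if its second time point is Week 6. The other, a multi-visit interaction, would not target Week 6, and under the assumptions above it would be significant about 97 to 98% of the time for a benefit that has vanished by then.

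The gain from baseline adjustment is real but conditional: a variance ratio of 0.65 to 0.85 with equal SDs, about 0.78 to 1.0 if the entry cut compresses baseline, and power of about 0.94 to 0.98 instead of 0.91 at the back-solved SD of change. The SDs and correlations are assumptions, not figures from the article. In large samples the adjusted contrast is never less precise than the change-score test that was powered. This should be changed, but it does not make the planned analysis invalid.

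**What to change.** In Major endpoints, define the primary outcome as change in CAPS past-week score from baseline (Visit 3) to Week 6 (Visit 9). In Primary analysis, name one primary test at 0.05: the drug-minus-placebo difference at Week 6 from the mixed model, with Visit 3 CAPS as a covariate. List the model factors there, so that the cross-reference under Response rates has something to refer to. State that the overall group-by-time interaction and the comparisons at Weeks 1, 2 and 4 are supportive. Under Statistical power/sample size, say that the second time point is Week 6.

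Further model detail (baseline-by-visit, site, an unstructured covariance) is optional and can go in the analysis plan. The cost is wording only: no new data, visits or participants. It should be done before unblinding.

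### Response is defined at each woman's last on-drug visit but analysed visit by visit and averaged; remission has only the last-on-drug rule, which acts as carry-forward for early stoppers

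*Protocol article*

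**What the plan says.** All references are to the protocol article.

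- **Major endpoints** names response and remission as secondary outcomes and gives each woman one status. For response: "Response is defined as ≥ 50% reduction from the baseline CAPS total score at the final on-drug study visit (V9 for completers". For remission: "Remission is defined as a CAPS score ≤ 20 at the final on-drug visit". The parenthesis about completers shows that for other women the visit is an earlier one.
- **Response rates** (under Secondary aims) describes a binary mixed model in which "at each time point, a subject will be classified as a responder if there is at least 50% improvement in CAPS". It adds: "This analysis is an averaged group comparison of time-point specific response rates, and thus a patient can change response categories over time". A group-by-time interaction is expected, with post hoc tests at each time point. Remission is not mentioned there.
- **Primary analysis** sets the general approach: intent-to-treat, with a "likelihood-based, mixed effects model that assumes any missing data meet the missing at random (MAR) assumption". Secondary outcomes go into a false-discovery-rate adjustment.
- **Study assessment visits**: "Symptom severity ratings are performed at weeks 1, 2, 4, and 6 post-randomization". Table 1 agrees (V4, V5, V6, V9) and shows no CAPS at V7 or V8.
- **Statistical power/sample size** expects 35% dropout among 154 randomised women.
- **Follow-up period** brings early stoppers back 7 days and 1 month after the last dose. It states no week-6 visit for them.

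**The concern.** The two sections describe different quantities under one name. Major endpoints gives a single status per woman, taken whenever her treatment ended. Response rates gives a status that may change from visit to visit and is averaged over visits; no final on-drug visit enters that model. An analyst following one section and an analyst following the other could report different response results, and either could enter the false-discovery adjustment.

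The last-on-drug rule also has a property of its own. A woman who stops after week 1 is classified from week 1, when less of any improvement has had time to appear. Where response rates rise over time, the proportion responding then depends on how long women stayed on treatment as well as on the drug. This matters most for remission, where no other definition is given.

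**Working it through.** **1. The plan's own figure.** 50 completers per group / (1 − 0.35) = 76.9, rounded up to 77 per group and 154 in total. This matches the article. Women expected to be classified before week 6: 0.35 × 154 = 53.9, about 54.

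**2. The definitions side by side.**

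| | Major endpoints | Response rates |
|---|---|---|
| Status per woman | one | one per visit |
| Time point | last on-drug visit; V9 for completers only | weeks 1, 2, 4, 6 |
| Early stopper | keeps the week 1, 2 or 4 status | later visits missing, handled under MAR |
| Group comparison | none stated | averaged over visits, with tests by time point |
| Covers remission | yes | no |

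**3. Can the two differ in size?** The documents give no response rates, so these are **assumed** for weeks 1/2/4/6: placebo 5/12/25/35%, drug 7/18/38/50%. Stops are spread evenly over weeks 1, 2 and 4 and are unrelated to response.

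Formula: last-on-drug rate = (1 − d) × week-6 rate + d × mean of the week 1, 2 and 4 rates, where d is the dropout proportion.

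- Mean early rates: placebo (5 + 12 + 25)/3 = 14%; drug (7 + 18 + 38)/3 = 21%.
- Week 6: 50 − 35 = **15.0 points**.
- Last on drug, d = 0.35 in both arms: placebo 0.65 × 35 + 0.35 × 14 = 27.65%; drug 0.65 × 50 + 0.35 × 21 = 39.85%; difference **12.2 points**. With mostly early stopping it is 11.3, with mostly late stopping 13.2.
- Simple average over four visits: placebo 77/4 = 19.25%; drug 113/4 = 28.25%; difference **9.0 points**. This only approximates the averaged comparison, because the planned model works on its own link scale.

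**4. No drug effect (both arms on the placebo rates).** The last-on-drug difference is −(d_drug − d_placebo) × (35 − 14).

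- Equal dropout: 0.
- 45% drug versus 25% placebo: −0.20 × 21 = −4.2 points. Swapping the arms gives +4.2.

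**5. A second set of assumptions, by simulation (200,000 per arm).** Baseline CAPS about 78 (SD 14), cut at 50. Mean fall by week 6 is 24 on placebo and 31 on drug, reached 35/55/80/100% at weeks 1/2/4/6. The SD of fall between women is 16 and the residual SD is 8. Dropout is either non-informative or related to the last observed change. Women with no on-drug CAPS are either excluded or counted as non-responders; dropout type and this choice together produce the ranges.

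- Week-6 response 33% versus 21%, difference 12.1 points.
- Last on drug, 35% dropout in both arms: 8.6 to 9.8 points, so 2.3 to 3.5 points lost.
- No drug effect, 45% drug versus 25% placebo: −2.3 to −3.6 points.

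Both sets of assumptions give the same pattern.

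**The case against.** The strongest reply is that the one response analysis described freezes nobody. It is a likelihood-based mixed model under MAR in which status may change, so carry-forward bias belongs to an analysis that the article does not describe for response. That stands. A reader might infer that the secondary results are biased as planned; the documents do not support this. Bias arises only if the last-on-drug status is itself analysed and a week-6 effect is the target. Status at the end of treatment is also a legitimate quantity if declared as such, though Major endpoints does not declare it.

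Other stronger readings also fail:

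- *The rule contradicts the intent-to-treat and MAR approach.* It does not. One passage defines an endpoint and the other a way of modelling missing data, and a last-on-drug status can be computed for nearly every randomised woman.
- *Remission is contradicted too.* It has one definition and no competing analysis in the article. Its model may sit in the full plan, which is not shown.
- *Women whose last visit is V7 or V8, or who stop before V4, cannot be classified.* The natural reading is the last on-drug visit with a CAPS. An early-termination rating, and the handling of women with no on-drug CAPS, are details that an article commonly leaves out.
- *The response groups under Assessment of confounders become completer and stopper groups.* That section does not say which response definition it uses.

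The illustrations are also open to challenge. The documents supply only the 7-point difference and the 35% dropout. The simulation's SD of change is at least √(16² + 8²) = 17.9, whereas power of 0.91 with 50 per group implies about 7 / [(1.960 + 1.341) × √(2/50)] = 10.6 (two-sided 0.05 assumed). Nothing in the documents predicts unequal dropout.

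What survives is that two definitions of a named secondary outcome are stated and not reconciled.

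**Conclusion.** The point holds in a limited form. Response has two definitions in the article, the one defined is not the one analysed, and they can give different effects from the same data. Remission has only the last-on-drug rule. For the expected 35% who stop early, that rule is last observation carried forward from week 1, 2 or 4, unless an unscheduled rating exists that the article does not describe.

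If the last-on-drug status is read as a week-6 effect, then under the assumed trajectories about 2 to 4 points of a 12 to 15 point difference are lost at equal dropout. At 45% versus 25% dropout with no drug effect, a false difference of about 2 to 4 points appears, its sign set by which arm loses more women. With equal dropout and no drug effect there is no false difference. These figures require response rates that rise over time and cannot be fixed from the documents. The primary outcome, its significance level and the sample size are not touched.

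**What to change.** - In Major endpoints, define response and remission at Week 6 (V9) for all randomised women, and align Response rates with that.
- Name one Week 6 arm contrast per endpoint as the test that enters the false-discovery adjustment, estimated under the plan's own MAR assumption. Either route will do: the Week 6 contrast from the mixed model already planned, which includes tests by time point, or imputation of continuous past-week CAPS followed by the 50% and 20-point cuts. State the choice for remission as well as response.
- Keep the last-on-drug version as a labelled sensitivity analysis, using the last on-drug visit that has a CAPS rating.

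The cost is wording in two sections and, if imputation is chosen, a routine extra step. No new data, visits or patients are needed. The downside is that early stoppers' Week 6 status then rests on the MAR model, since the article states no week-6 visit for them, and intervals will be slightly wider.
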